### Intervention

#### Self-Help plus (SH+)

The participants in the experimental arm will receive SH + and ECAU (see the ECAU section below). SH + is a five-session, group-based (20–30 people) stress management intervention for adults [20]. The five sessions last 90–100 min each and take place once a week for a total of five weeks. SH + consists of a pre-recorded audio course and an illustrated self-help book called Doing What Matters in Times of Stress: An Illustrated Guide. SH + is delivered by two trained facilitators.

SH + was developed based on Acceptance Commitment Therapy (ACT). It consists of five core skills described in the book Doing What Matters (DWM) in times of stress: (1) grounding (bringing our attention to the present moment); (2) unhooking (unhooking from difficult thoughts and feelings); (3) acting on your values (identifying personal values and acting based on those values); (4) being kind (being kind to oneself and others); and (5) making room (making a room for difficult thoughts and feeling, instead of fighting with them). The participants are not expected to share much personal information with each other or with the facilitator. They focus on learning self-help skill to manage stress [20].

The audio material contains key information on stress management and guides participants through individual exercises and small group discussions [52]. The self-help book entitled *Doing What Matters in Times of Stress: An illustrated Guide* [21] reviews all essential content and concepts. A copy of the book will be provided for each participant. The SH + facilitators will guide participants during each group session by playing the audio, reviewing the skills introduced by the audio, providing culturally relevant examples and clarifications, and reading out discussion questions to make the groups interactive [20].

Before being tested, the SH + intervention underwent adaptation to ensure its acceptability and relevance to the context, as recommended by the WHO. This process followed the WHO guidelines for adapting interventions [53]. This adaptation process included a rapid qualitative assessment, for which we interviewed students, stakeholders, and mental health professionals within the university. The adaptation consisted of the language, visuals, examples, and metaphors used in the illustrated book, audio, and facilitator manual. Further details about the adaptation process will be provided in a separate paper.

#### Enhanced care as usual (ECAU)

Enhanced care as usual (ECAU) consists of an e-leaflet containing information about support services at the university. This includes options for individual counselling and peer counselling and instructions on how to schedule an appointment. Other information includes mental health services outside universities and emergency contact for mental health issues.

#### Contamination

To minimize the risk of contamination, we implemented several measures: During the first session, participants in the SH + group are explicitly asked not to share or discuss the intervention materials with others outside the SH + group. We do not explicitly restrict the control group from independently accessing the SH + materials on the WHO website. Therefore, to know if they were accessing the material, during the T2 and T3 we ask them about whether they knew about the SH+ (see other measures above).

#### Facilitators

SH + will be delivered by two facilitators (a pair), and each university will have two to four facilitators. SH + facilitators have at least a bachelor’s degree in psychology. Individuals with a bachelor’s degree in psychology and who are currently in training to become a psychologist can be a facilitator.

There will be open recruitment to become a facilitator, and recruitment will start during the preparation of the study and before the recruitment of the study participants. The facilitator will receive up to 40 h of training based on the SH + training manual [54], and the total number of hours will depend on the skills and experience of the facilitators already has. The training will be conducted by the coordinator of this study (DA) or a clinical psychologist who has been trained by the coordinator of this study. The training will consist of basic helping skills, SH + facilitating skills, and managing participants’ distress, explaining the aims and background of the SH + intervention.

In addition to delivering SH+, the facilitator will be the one to contact participants to inform them of their randomization allocation. The facilitator will deliver the ECAU (i.e., leaflet) to all participants via email or media communication of the participant’s choice.

The clinical supervisor and facilitator will receive remote support and supervision from the research coordinator as needed. The facilitator will have an online group meeting with the supervisor who is a clinical psychologist to discuss protocol adherence, review barriers or potential barriers, facilitator concerns, any adverse effects and serious adverse events.

#### Treatment fidelity

Treatment fidelity will be assessed in various ways. First, after finishing each session, the facilitator will complete the SH + post-session review form [20] and a fidelity checklist form, which consists of a list of the main activities of each SH + session. Second, the facilitator will record the session of SH+, and the recording will be assessed with the fidelity checklist by the research coordinator.

### Analysis

#### Sample size

By utilizing G*Power [55], considering psychological distress as the primary outcome with an effect size of 0.3, a power calculation for a repeated measures design suggests a minimum sample size of *N* = 148 (power = 0.95, α = 0.05, rho = 0.9) to detect the expected effect size. Accounting for a 50% attrition rate observed during our pilot, a total of 296 participants will be recruited (148 participants in each arm). At each university, there is an intervention group and a control group. Each group will consist of 20–30 participants.

#### Data analysis

Data will be analysed once all data has been collected; no interim analyses will be performed. However, participants can withdraw from the study or the session anytime without giving a reason.

**Quantitative data (RCT).** An intention-to-treat (ITT) approach will be used to conduct data analysis both in primary and secondary outcomes, and the unit of the analysis is individual. The primary analysis will simultaneously assess the treatment effect on the mean PHQ-ADS total score at each time point. All participants randomized to either group will be analysed, regardless of whether they complete the intervention. The ITT population will consist of all participants randomized to the competing intervention strategies who have at least baseline assessment data available. The main conclusion of the trial will be based on the ITT analysis of the primary outcome (i.e., the effect on the PHQ-ADS score at the three-month follow-up).

Adherence will be defined based on attendance at least three sessions of SH+. A per protocol (PP) approach will be used to test the robustness of the intervention results for all outcomes, which will include only SH+/ECAU participants who attend at least three sessions of the SH + intervention [24]. The attendance of the participants will be recorded by the facilitator(s) of the SH+.

Linear mixed models will be used for the PHQ-ADS (primary outcome) and secondary outcomes to evaluate the treatment effect on all endpoints at t2, t3 and t4, with time as a fixed effect, baseline PHQ-ADS score as a covariate and participants as random effects. A t-test will be used to analyse the differences between the two study arms. Multiple imputation will be used to handle the missing values at 3 months. A sensitivity analysis will be conducted to compare the full sample with the sample that excludes ECAU participants who indicated being exposed to SH + materials.

A health economic analysis will be conducted to assess the cost-effectiveness of SH+/ECAU compared with ECAU only, from both a health system and a societal perspective. The results of this analysis will be expressed as incremental cost-effectiveness ratios (ICERs) per quality-adjusted life years (QALYs) gained and per change in the PHQ-ADS composite score at the *t*_*3*_ follow-up assessment point (3 months). QALYs will be estimated using the EQ-5D-5 L questionnaire adapted to the Indonesian value set [46]. A deterministic sensitivity analysis will be performed to identify the most sensitive parameters affecting the ICER. The cost-effectiveness thresholds will follow the current guidelines for Indonesia, which is 1–3 times GDP per capita. The difference and QALY difference between the two groups will be estimated using generalized linear regression. The skewed distribution of the cost data was accounted for by estimating robust standard errors using the Huber-White sandwich estimator.

**Qualitative data (process evaluation). The** Interviews and FGDs will be audio recorded and transcribed verbatim. Thematic analysis will be carried out using ATLAS.ti [56].

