## Goals and hypotheses

The primary objective of the study is to evaluate the effectiveness and cost-effectiveness of a culturally adapted SH + intervention combined with ECAU among university students in Indonesia at a three-month follow-up (main time point) in reducing psychological distress. The secondary objectives are to assess depression and anxiety symptoms separately, as well as perceived stress, functioning, quality of life, resilience, identified problems, feasibility, and acceptability. In addition, moderator variables influencing the reduction in psychological distress, anxiety, and depression symptoms and improvements in functioning and quality of life will be explored.

Previous research on SH + among South Sudanese female refugees in Uganda found that SH + reduced psychological distress three months after the intervention [22]. In addition, a follow-up period of three months is long enough to observe the sustained effects of the intervention while minimizing loss to follow-up and recall bias. In the context of our university student population, a three-month timeframe also aligns with academic terms, thereby reducing the risk of attrition due to changes in academic circumstances or different types of activities. For example, some students may have to enrol in an internship programme or live in a rural community for a full semester. Therefore, we expect that SH + with ECAU (SH+/ECAU) will be superior to the ECAU only in reducing psychological distress (primary outcome) at three-month follow-up, as well as the secondary outcomes of depression and anxiety, perceived stress, improved functioning, quality of life, resilience, and identified problems. Furthermore, we expect that SH+/ ECAU will report lower healthcare costs than ECAU-only.

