#### Assessment

Data will be collected through self-report assessments at four times points: *t*_*1*_ (baseline – sent at least 10 days before the SH + to the participants already enrolled), *t*_*2*_ (post-SH+, week-7), *t*_*3*_ (main time point – 3 months after SH+), and *t*_*4*_ (follow-up – 6 months after SH+) with the Castor Electronic Data Capture (EDC) software program [33]. Each assessment will be provided via e-mail with a link to the self-report questionnaire to each participant and can be completed on any device with internet access. The time to complete each assessment is approximately 20–30 min. If an assessment remains incomplete, the participant will receive a maximum of three reminders on days 3, 7, and 10 through various communication channels to encourage retention. The participants will receive IDR 50,000 e-money for each completed assessment, with a maximum of four e-money awards (*t*_*1*_ to *t*_*4*_).

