### Trial monitoring and adverse events reporting

(Serious) adverse events ((S)AEs) are defined as any undesirable experience that a participant has during the study, regardless of whether it is related to the study procedure or the SH + program. All SAEs will be recorded in Castor EDC and reported to the Research Ethics Committee of Universitas Padjadjaran. The research team will follow up with all SAEs until they are stabilized or resolved. If necessary, participants will be referred to a general practitioner. Participants may withdraw from the study at any time. No withdrawal criteria are specified.

To support participants who may require additional mental health care, we collaborate with the University Counselling Centre and have established a referral procedure. In this study, the research assistants have been trained to familiar with the mental health facilities available and know how to refer participants to the University Counselling Centre.

This study involves several potential risks, including emotional distress triggered during sessions and, in some cases, suicidal thoughts. To mitigate these risks, we have implemented a clear referral protocol for participants who express suicidal thoughts or severe distress. Facilitators are trained to respond sensitively and involve mental health professionals when necessary. Participants are informed of these procedures during the consent process and reminded that they can withdraw at any time without consequence.

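### With half the sample expected to be lost, a paid 16-item fallback at three months would be a cheap way to recover primary-outcome scores

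*Protocol article*

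**What the plan says.** Sample size (protocol article): "a power calculation for a repeated measures design suggests a minimum sample size of *N* = 148", followed by "Accounting for a 50% attrition rate observed during our pilot, a total of 296 participants will be recruited", that is, 148 per arm.

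Assessment: each time point is one e-mailed self-report battery. On its length: "The time to complete each assessment is approximately 20–30 min". On payment: "The participants will receive IDR 50,000 e-money for each completed assessment", with at most four awards. An incomplete assessment triggers no more than three reminders, on days 3, 7 and 10, through various channels.

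Primary outcome measure: PHQ-ADS at three months is the sum of PHQ-9 and GAD-7. Table 1 places these two scales alongside PSS, WHODAS 2.0, EQ-5D-5L, MIMIS, PSYCHLOPS and CSRI at every assessment.

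Data analysis: "participants can withdraw from the study or the session anytime without giving a reason". Everyone randomized with baseline data is analysed whether or not they complete the intervention, by mixed models with multiple imputation at three months. The main conclusion rests on PHQ-ADS at three months. The section on trial monitoring adds: "Participants may withdraw from the study at any time. No withdrawal criteria are specified".

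**The concern.** The trial's own pilot leads it to expect that half the participants will be lost. The stated collection procedure puts the few items that carry the main conclusion inside a much longer battery, pays for finishing an assessment, and ends contact after the third reminder. The article describes no step that asks someone unwilling to do the whole battery for the 16 items alone.

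Recruiting twice as many people restores the planned number of observed scores. It does not make those who stay representative of those who leave. The mixed model and the imputation can adjust for what was measured, but both assume missingness at random, here for about half of the primary scores. An observed score removes the need for that assumption for the person who gave it.

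The arms also differ in contact: five weekly group sessions against an e-leaflet. Different loss by arm is therefore plausible, although no figure in the article shows it.

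**Working it through.** **Inputs.** Minimum analysed total 148, attrition 50%, recruited total 296, effect size 0.3 (Sample size). PHQ-9 has nine items and GAD-7 seven (Secondary outcome measure). Battery length, payment and reminders are as in Assessment. The share of non-responders who would answer a short form is not in the article and is assumed below.

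**1. The plan's own figure.** 148 / (1 − 0.5) = 296, reproduced exactly. The base of 148 is reproduced by a two-group F test with f = 0.3, two-sided α = 0.05 and a single measurement (power 0.952). The article does not say whether 0.3 is f or d, so the gain is expressed below as a standard error, which does not depend on that choice.

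**2. Size of the primary outcome.** 9 + 7 = 16 items.

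**3. Expected scores without a fallback.** 296 × 0.5 = 148 observed and 148 missing, or 74 and 74 per arm if loss is equal.

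**4. Effect of a fallback on precision.** Let r be the share of the 148 losses recovered. Observed n = 148 + 148r. The ratio of standard errors based on observed scores is √(148/n).

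| r (assumed) | Extra scores | Observed n | Loss | SE ratio | SE reduction |
|---|---|---|---|---|---|
| 10% | 14.8 | 162.8, about 163 | 45% | √(148/162.8) = 0.953 | about 5% |
| 20% | 29.6 | 177.6, about 178 | 40% | √(148/177.6) = 0.913 | about 9% |
| 30% | 44.4 | 192.4, about 192 | 35% | √(148/192.4) = 0.877 | about 12% |

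**5. Effect on bias.** Suppose loss is equal in both arms, and the arm difference among those missing departs from that among those observed by D. The estimate from observed scores is then off by (fraction missing) × D. Take D = 0.3 SD for illustration; the article gives no value.

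- No fallback: 0.5 × 0.3 = 0.15 SD.
- If those recovered resemble those still missing, D is unchanged in the remainder. The error becomes 0.45 × 0.3 = 0.135, 0.40 × 0.3 = 0.12 or 0.35 × 0.3 = 0.105 SD at 10%, 20% or 30% recovery.
- If those recovered resemble the completers, the observed estimate does not move and the error stays at 0.15 SD.

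This formula describes an analysis of observed scores. The planned imputation and mixed model would remove whatever part of D is explained by measured variables.

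**The case against.** The strongest objection is that the article states nothing wrong here, and that operational follow-up detail commonly sits in a fuller protocol. Much of that stands, and it rules out several stronger readings that a reader might infer.

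- *That participants must finish the whole battery or lose their primary score.* No sentence discards partial answers or says that saved PHQ-9/GAD-7 responses go unused. Table 1 lists these two scales first among the outcome instruments, which at least does not suggest that they come last.
- *That stopping the sessions ends data collection.* Assessments go to every participant with no condition on attendance, and everyone is analysed whatever they completed. The withdrawal sentence itself names study and session as separate things.
- *That doubling recruitment is the only answer to attrition.* Reminders, e-money, imputation and the choice of time point are answers too.
- *That the rationale for three months contradicts the 50% allowance.* Choosing a time point with a view to "minimizing loss to follow-up and recall bias" is compatible with budgeting for heavy loss.
- *That a short form would recover a large, known share.* The article does not say whether the pilot's 50% was missed assessments or missed sessions. People who ignored three reminders may also ignore a fourth message.

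The procedure that is stated remains open to improvement. The Assessment section gives the battery length, the payment condition, and the number and days of reminders. Against an expected 50% loss, those stated choices leave out an inexpensive step. Dated exit categories and item ordering, by contrast, are detail that an article may leave elsewhere, and they are not part of this point.

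**Conclusion.** The point holds as a cheap improvement to the Assessment section, prompted by the attrition figure in Sample size. It is not an error or a contradiction. With 148 of 296 three-month scores expected to be missing, inflation protects the sample count but not against selection, and the planned methods lean on missingness at random for about half of the primary data.

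A fallback limited to the 16 items would add about 15, 30 or 44 scores and lower the standard error by about 5%, 9% or 12%, if 10%, 20% or 30% of the expected losses answered it. Those shares are assumptions. They also take the pilot's 50% to be lost assessments. If it was lost attendance, fewer scores would be missing and the gain would be smaller. The reduction in bias is less certain than the gain in precision, and may be nil if those recovered are like the completers.

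**What to change.** In the Assessment section, add that after the day-10 reminder at three months every non-responder in either arm is sent a Castor link containing only the PHQ-9 and GAD-7 items, with the same e-money for completing it. State also that PHQ-9 and GAD-7 answers already saved in a partly completed battery will be used for the primary outcome. The procedure must be identical in both arms. It would help to state whether the pilot's 50% refers to assessments or to attendance.

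Cost: one short form and one extra automated message, with no added staff. At 10%, 20% or 30% recovery the payments are about 15, 30 or 44 × IDR 50,000 = IDR 750,000, 1,500,000 or 2,200,000. The short form takes the place of the three-month award, so the maximum of four awards per person is unchanged.

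Downsides: short-form responders have no other secondary outcomes at three months, although these would probably have been missing anyway. There is also a small risk that some participants wait for the short form. Not announcing it in advance would limit that.

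### SH+ is delivered in shared groups, but the stated model and sample size have no group term: if outcomes correlate within SH+ groups, the type I error exceeds 5%

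*Protocol article*

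**What the plan says.** **Delivery.** Under Randomization, individual participants are allocated 1:1. Under Self-Help plus (SH+), the intervention is a five-session, "group-based (20–30 people) stress management intervention for adults" with small-group discussions. Under Facilitators, "SH + will be delivered by two facilitators (a pair), and each university will have two to four facilitators". The comparator shares no sessions: "Enhanced care as usual (ECAU) consists of an e-leaflet containing information about support services at the university".

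**Analysis.** Under Data analysis, the intention-to-treat approach "will be used to conduct data analysis both in primary and secondary outcomes, and the unit of the analysis is individual". The linear mixed model is specified "with time as a fixed effect, baseline PHQ-ADS score as a covariate and participants as random effects", and a t-test compares the two arms. No term for session group or facilitator pair appears for any clinical outcome. The Huber-White estimator in the health economic paragraph is there for skewed costs.

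**Sample size.** The inputs are an effect size of 0.3 (metric not named), power 0.95, α 0.05 and rho 0.9, giving a total of 148. Allowing for 50% attrition gives 296, or 148 per arm. No ICC or design effect is given, although the same paragraph says "Each group will consist of 20–30 participants".

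**The concern.** This is an individually randomised trial with group treatment in one arm. Randomisation makes participants independent at baseline. Those in the SH+ arm then share sessions, discussions and a facilitator pair, and any similarity that this creates arises after randomisation. A participant random effect covers repeated measures within a person. It does not cover similarity between people in the same group.

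If such similarity exists, the SH+ arm mean varies more than the model allows. Confidence intervals are then too narrow, and the error runs towards a false claim of superiority on the outcome that carries the trial's main conclusion. The precision of the SH+ mean would also depend partly on the number of groups, which is small.

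This is not detail left to a later analysis plan. The article itself names the random effects and the test, so an analysis plan that followed it would carry the omission forward.

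**Working it through.** **1. Reproduce the plan's figure.** Two groups of independent participants, one measurement, f = 0.3, α = 0.05, noncentral F with λ = f²N:
- N = 146: power 0.9496
- N = 148: power 0.952, the first even N to reach 0.95
- 148 / (1 − 0.5) = 296

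So 148 and 296 reproduce with 0.3 read as Cohen's f (d = 2f = 0.6) and no clustering. That reading is an inference.

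**2. Number of SH+ groups.** 148/30 = 4.9 and 148/20 = 7.4, so about 5 to 8. Two universities with two to four facilitators each give 4 to 8 facilitators, or 2 to 4 pairs if pairs are fixed. The group count is not stated. Sample size also describes one intervention group and one control group at each university. Read literally, that is two SH+ groups, or 40–60 people, which does not fit 148 per arm.

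**3. Type I error of the unclustered test.** Clustering is in the SH+ arm only, with equal arms, m analysed per group and total variance 1:
- SH+ arm design effect: D = 1 + (m − 1) × ICC
- variance ratio of the arm difference: R = (1 + D)/2
- true two-sided error: 2 × [1 − Φ(1.96/√R)]

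Example, m = 12 and ICC 0.05: D = 1 + 11 × 0.05 = 1.55; R = 1.275; √R = 1.129; 1.96/1.129 = 1.736; error 8.3%.

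The ICC is assumed. The value m = 12 is a group of about 25 after the planned 50% attrition. The value m = 25 is the same group with none.

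| ICC | m = 12: D | error, formula | error, simulated (6 groups, 74 controls) | m = 25: D | error, formula | error, simulated (6 groups, 148 controls) |
|---|---|---|---|---|---|---|
| 0 | 1 | 5.0% | 5.0% | 1 | 5.0% | 5.1% |
| 0.01 | 1.11 | 5.6% | 5.6% | 1.24 | 6.4% | 6.3% |
| 0.02 | 1.22 | 6.3% | 6.2% | 1.48 | 7.8% | 8.2% |
| 0.05 | 1.55 | 8.3% | 8.2% | 2.20 | 12.1% | 11.9% |
| 0.10 | 2.10 | 11.5% | 11.8% | 3.40 | 18.6% | 18.5% |

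Simulations used 40,000 runs (m = 12) and 20,000 runs (m = 25). Repeat runs differ by a few tenths of a point.

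**4. Power of a valid test.** The same simulation with d = 0.6, 6 groups of 12 and 74 controls compares SH+ group means with individual controls, using Satterthwaite degrees of freedom:

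| ICC | power | type I error |
|---|---|---|
| 0 | 0.92 | 5.0% |
| 0.01 | 0.90 | 5.1% |
| 0.02 | 0.89 | 5.0% |
| 0.05 | 0.83 | 5.2% |
| 0.10 | 0.75 | 5.3% |

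The test holds its level. The drop from 0.95 to 0.92 at ICC 0 is the cost of having few groups, and the rest is clustering.

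**The case against.** **No ICC is given, and some features point to a low one.** The course is pre-recorded audio with a book, includes individual exercises, and does not expect much personal sharing. The intention-to-treat set also keeps people who attend little or nothing. This stands. A reader might infer that the type I error certainly exceeds 5%, but the article does not support that. At ICC 0 it is 5%, and at 0.01 with attrition about 5.6%. The same section also describes small-group discussion and facilitators who add examples and try to make groups interactive, so zero correlation cannot be presumed either.

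**The 12% and 18–19% figures are not the expected case.** They need 148 observed outcomes per arm, against a planned attrition of 50%. Multiple imputation does not turn missing outcomes into observed ones. This stands, and those figures are an upper bound.

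**A reader might use rho = 0.9 to argue for a larger effect.** If rho were the baseline–follow-up correlation, adjustment would leave 1 − 0.81 = 19% of the variance, and a raw ICC of 0.02 would become roughly 0.10. The article does not say which correlation rho is, so this cannot be relied on.

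**The power figures are not those of the planned model.** They leave out the baseline covariate and repeated measures, and they rest on reading 0.3 as Cohen's f. Both limits stand. Even so, power stays at about 0.83 or more up to ICC 0.05, so the sample-size part alone would not be serious.

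**An individual unit of analysis is correct under individual randomisation.** That is true, and it stays true under the remedy. The defect lies in the list of random effects and in the t-test.

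**Conclusion.** The concern holds in conditional form. The article describes group delivery in one arm and fixes an analysis and a sample size that ignore it. If the ICC within SH+ groups is positive, standard errors are too small and the type I error exceeds its nominal 5%. The excess is minor at ICC 0.01–0.02 under the planned attrition and material from about 0.05. The type I error has no reserve to absorb it, whereas the planned power of 0.95 does have some.

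The size rests on an assumed ICC of 0.01–0.10, about six SH+ groups (inferred) and equal group sizes. The power figures also need 148 completers and d = 0.6. Because the main conclusion rests on this test and the trial had not started at the reported status date, the model should be corrected before analysis.

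**What to change.** **Data analysis.** Specify a partially nested linear mixed model for all clinical outcomes. It has a random session-group effect in the SH+ arm only (each ECAU participant a cluster of one) alongside the participant random effect, with Satterthwaite or Kenward-Roger degrees of freedom. Use it in place of the t-test. Record session-group ID and report the estimated ICC.

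**Sample size.** Name the effect-size metric. Restate power over a stated ICC range, for example 0.01–0.05, with the design effect in the SH+ arm only and allowance for the small number of groups. State the planned number of SH+ groups, and reconcile it with the sentence that describes one intervention group and one control group per university. Enrolling more participants is not needed for this correction.

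**Cost.** A change of wording and one extra variable; facilitators already record attendance. Confidence intervals become somewhat wider and the stated power lower. With only 5 to 8 groups the group variance is estimated imprecisely, so the reported ICC will be uncertain.
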